**Fig. 1 Fig1:**
[figure not shown]
The STAY Fit Trial schedule of enrollment, interventions, and assessments

All participants who express interest will be provided with a description of the study and screened for eligibility. All participants will be required to read and sign a University Institutional Review Board-approved informed consent prior to study participation and data collection. Upon enrollment in the study, each participant will be assigned a random unique identification (ID) number as the only way to match collected data to their identifiable information. An electronic database, stored on a secure password-protected network only accessible by the study investigators, will house the key linking participant information and ID number. All written hard copies of participant data collected during the study period will only have the ID number written on them and will be stored in a secure location on the research site. Upon completion of the study, the key linking ID numbers and participant information will be destroyed. Participants will be informed that their de-identified data may be made available to regulatory authorities or ancillary individuals from the university, upon reasonable request. A snapshot of the flow of participants through the STAY Fit study is presented in Fig. 2.

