### Randomization

Participants who are eligible for the study and complete all baseline measurements will be randomly assigned to 1 of the 3 intervention arms using a computer-generated program. Randomization will take place in groups following rounds of advertising and is stratified based on sex, age, and years since cancer diagnosis. Couples or friends who sign up for the study together will be randomized together to avoid contamination across groups. Randomization will take place following completion of all baseline assessments and a week before the 12-week exercise sessions are scheduled to begin. Participants will be notified via a mailed letter and follow-up phone calls confirming their randomized group and logistics (parking and directions) for their 12-week exercise sessions. This is an open label trial with no blinding of participants or assessors.

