### Measures

All measures will be assessed at baseline and following the 12-week intervention. Measures of cognitive function (primary outcome) and cardiovascular function (secondary outcome) will be conducted in the laboratory by trained research assistants across two lab visits lasting approximately 2 h each. A battery of psychosocial questionnaires will be given to the participant to complete at home along with an Actigraph accelerometer (wGT3X-BT) that participants will be asked to wear for 7 days and nights to record objective levels of physical activity and sleep quality. We will schedule the testing appointments 1 week apart, so participants have time to complete the questionnaire packet and wear the accelerometer before returning to the lab.

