#### Cognitive function (primary outcome)

The primary outcome of the trial is cognitive function. Specifically, we will measure executive function, attention and processing speed, memory, and working memory using the tests presented in Table 1. These measures have been used in the exercise-cognition literature and are partly adapted from the NIH Toolbox. The tasks are computer- and paper-based and will be administered over the two testing sessions on separate days and repeated again after the 12-week intervention. The first testing session consists of immediate and delayed word recall [18], flanker task [19], spatial working memory [20, 21], trail making [22], and matrix reasoning [23] task. The second session consists of relational memory [24], pattern comparison [25], and task switching paradigm [14, 21]. All measures involve a practice phase that explains the task instructions and allows participants to familiarize themselves with the test.

**Table 1 Tab1:** Battery of neurocognitive tests administered at baseline and follow-up

Cognitive test	Cognitive domain	Approximate test duration
Word list (immediate and delayed recall)	Short- and long-term memory	5 min
Flanker task	Attention and inhibitory control	8 min
Spatial working memory	Spatial memory	15 min
Trail making A and B	Visual scanning, mental flexibility, processing speed	5 min
Matrices	Fluid intelligence	10 min
Spatial reconstruction task	Relational memory	Self-paced, 20 trials
Pattern comparison	Processing speed	4 min
Task switching	Mental flexibility	15 min

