### Exercise intervention and active control groups

#### Yoga arm

The yoga intervention consists of two weekly, 90-min group sessions for 12 weeks. The style of yoga selected for the intervention is Hatha yoga, the most popular form of yoga practice in the USA [28] which focuses on practicing physical poses, breathing, and meditation. STAY Fit yoga sessions will be held at a local yoga studio and taught by a certified yoga instructor, who has been instructing and practicing for more than 20 years. Each 90-min session is structured such that participants perform 60-min of stretching and poses (*asana*), 15 min of guided breathing practice (*pranayama*), and 15 min of guided meditation. Table 2 depicts a sample yoga session. Sessions are designed at a beginner level for the first few weeks, with a focus on helping participants develop good form, proper alignment, and postures for the asanas. Props used during the sessions include a yoga mat, chair, blanket, and blocks.

**Table 2 Tab2:** Sequence of Hatha yoga and stretching-toning exercises from week 1 of the STAY Fit Trial

Yoga	Stretching and toning
Poses (*asanas)*	Back arch
*Ardha Matsyendrasana*—twist in simple seated pose	Forward bend
*Marjaryasana/Bitilasana*—cat and cow	Squat
*Tadasana*—mountain pose	Military press
**Utkatasana*—chair pose	Walking dips
*Urdhva Hastasasana*—upward salute	Bicep + fly arm cycle
**Virabhadrasana*—warrior 1 and 2	Wood chop
**Purvottanasana*—intense side stretch	Tricep extension
*Viparita Karani*—Supported legs on the seat of a chair	One leg stand
*Supta Baddha Konasana*—reclining bound angle pose	Side leg abductions
*Supported Savasana*—corpse pose	Bicycle abdominal twist
Breathing (*pranayama*)	
3 parts breath in *Supta Baddha Konasana*	
Mediation	
Guided meditation/body scan while in supported *savasana*	

Note: *Using chair for support

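### The protocol rules out assessor blinding without giving a reason, although the primary outcome includes paper-based tests given after allocation, and at least their scoring could be masked cheaply

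*Protocol article*

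**What the plan says.** On blinding, the Randomization section is explicit: "This is an open label trial with no blinding of participants or assessors". This is a stated design decision, so a fuller document would not be expected to fill it in differently.

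On what is measured, the section on cognitive function says: "The primary outcome of the trial is cognitive function". Under Measures, the cognitive and cardiovascular assessments "will be conducted in the laboratory by trained research assistants across two lab visits lasting approximately 2 h each". On mode: "The tasks are computer- and paper-based and will be administered over the two testing sessions on separate days". Table 1 lists eight tests, among them word-list recall and trail making.

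On timing: "Randomization will take place following completion of all baseline assessments and a week before the 12-week exercise sessions are scheduled to begin".

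On who runs the sessions: "STAY Fit yoga sessions will be held at a local yoga studio and taught by a certified yoga instructor". The walking and the stretching and toning sessions are run by trained exercise leaders, who also record attendance.

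On records, the text under Recruitment procedures says: "All written hard copies of participant data collected during the study period will only have the ID number written on them". Only the study investigators can reach the key that links IDs to people.

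**The concern.** In a comparison of yoga, walking and stretching, participants cannot be kept unaware of their arm. That is no reason to leave outcome assessment unmasked as well. In examiner-given tests, the tester's instructions, prompts and timing, and the scorer's reading of an answer sheet, can shift with what that person knows and expects.

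The Statistical analysis section makes descriptive statistics and Cohen's d the focus. The Discussion says the results should help to inform a larger, fully powered efficacy trial. A systematic difference between arms in how tests are given or scored goes straight into d, and a larger sample does not remove it. If the procedure is carried over, so is the bias. The Background also says that the pilot is meant to test the feasibility of methods for a larger trial. Masked assessment, and how often it fails, is one such method.

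**Working it through.** The plan gives no figure on this point, so the check sets its statements side by side.

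1. **Is assessor blinding merely unmentioned?** No. Randomization rules it out in so many words. No reason appears there or elsewhere, and the section on strengths, limitations and future considerations discusses duration, the single follow-up and the submaximal fitness test, but not this.

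2. **When does the exposure arise?** All baseline assessments come before randomization. Baseline scores are therefore free of this problem, and only follow-up is open to it.

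3. **How would it reach the result?** Let *b*(arm) be the average shift in follow-up scores caused by knowledge of the arm.
   - Observed mean change = true mean change + *b*(arm).
   - Observed difference between yoga and control = true difference + [*b*(yoga) − *b*(control)].
   - Shift in d = [*b*(yoga) − *b*(control)] / SD.

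   Leniency that is equal in all arms cancels, and only a difference matters. Sample size does not appear in the last line. The documents give no value for any *b*.

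4. **Which measures are exposed?** The battery is part computer-based and part paper-based, but the article does not say which test is which. Word recall and trail making are usually examiner-administered. I assume that here; it is not stated. Computerised tasks leave less room for the tester. The treadmill test is a secondary outcome with fixed speed, fixed incline steps, a heart-rate end point and a formula for the result. Only users of beta-blockers stop on perceived exertion. It adds little to the concern.

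5. **Are testers and exercise leaders different people?** The role names differ (research assistants; exercise leaders; a certified yoga instructor), and so do the venues for testing and for yoga. The article never says that nobody does both. Separation is an inference.

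6. **Do the ID-only sheets provide masking?** Not for a tester who faces the participant. They would let someone else score a paper test without knowing the arm. The rule covers all hard copies, however, and so would appear to include exercise and home logs, whose content can reveal the arm. Scoring is masked only if test sheets are kept apart from those logs.

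7. **Is there another route to unmasking?** Yes. Under Adverse events and data safety monitoring, investigators and research staff review participant status every week.

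**The case against.** The best defence is that this is an openly declared choice in a small, single-site pilot that is meant to test feasibility and describe effect sizes. It contradicts nothing else in the article, and masking will be imperfect because participants can reveal their arm. All of that is true, and it limits the weight of the point. Disclosure does not remove bias, however, and effect sizes are what this pilot intends to pass on.

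Several stronger readings are tempting, and the article does not support them:

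- *Follow-up testers know the allocation.* The text says that assessors are not blinded, which means that they are not kept unaware. It does not say that each is told. The weekly reviews make knowledge plausible, no more.
- *Testing is already separate from exercise leading, so masked testing needs no extra staff.* This rests on role names alone. If the same people do both, masked testing could need more staff or a different organisation of the weekly meetings.
- *The bias would favour yoga.* The aims are comparative, and the Conclusions allow for yoga being comparable to walking. Only the cited meta-analysis favours yoga. The direction is not settled.
- *The bias is a large share of the expected effect.* One could assume a shift of 0.1 to 0.2 SD and set it against the 0.32–0.47 range under Sample size calculation: 0.1/0.47 = 21% and 0.2/0.32 = 63%. The numerators come from no document, so these percentages only restate the assumption.
- *The whole primary outcome is compromised.* Domains are analysed separately, and exposure differs by test.

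**Conclusion.** The point stands in a limited form. The protocol gives up assessor blinding without a reason, although part of its primary outcome is paper-based and is collected after allocation by research staff. Knowledge of the arm could affect how those tests are given and scored, and any difference between arms would go directly into the reported effect sizes. Neither the size nor the direction of the bias can be derived from the documents.

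The conclusion rests on one assumption: that at least some of the paper tests leave room for the examiner or scorer, as such tests usually do. It does not require that testers and exercise leaders are different people. Masked scoring and score construction can be arranged either way, provided the scorer works without the allocation, the logs or the participant present. Masked administration does depend on who is available, so it can be asked for only where rostering allows.

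**What to change.** Replace the blinding statement under Randomization with one to this effect: participants unmasked; outcome scoring masked. Then:

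1. Score the paper tests from sheets that carry only the ID, stored apart from exercise and home logs, by someone who does not have the allocation.
2. Build the domain scores before allocation codes are merged with the data.
3. Where existing rostering allows, have follow-up tests given by assistants who did not lead that participant's sessions, are not shown the allocation list and sit out arm-specific discussion in the weekly meetings.
4. Ask participants not to disclose their arm to the tester, and record each case of unmasking.
5. If masked testing is not feasible, say why and list it among the limitations.

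Steps 1 and 2 need separate filing and a fixed order of work, but no new staff. Step 3 puts a constraint on the roster and on the weekly meetings. Some unmasking will occur whatever is done; step 4 makes it visible and gives the larger trial a failure rate to plan with.

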### Sample size calculation

We recognize that pilot studies do not typically report formal sample size calculations. However, to aid us in making advertising and recruitment decisions, we ran a very preliminary sample size analysis to get an estimated range of subjects needed. A meta-analysis of yoga effects on cognition [13] indicated an effect size range of .32–.47 (Hedge’s g) favoring the yoga condition. We based our sample size calculations to adequately power for a small effect within this range. Using an alpha of 0.05/2, a power of 0.80, and a conservative estimate of a medium effect size (*f* = 0.35), the desired total sample size is 75 (*N* = 25 per group) for this trial.

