**Discussion:**

The STAY Fit Trial will test the effectiveness of yoga, aerobic exercise, and stretching and toning exercises in improving cognitive function and fitness among adult cancer survivors. The results of this pilot study will enable us to understand the most effective physical activity modality to improve cognitive function in this population and potentially combat cancer-related cognitive impairment.

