## Conclusions

In addition to advancing the science of yoga and contributing to the fields of integrative medicine, aging, neurocognition, and cancer survivorship, the results of this proposed randomized control trial could have a significant impact on health care recommendations for cancer survivorship. Our study will determine the efficacy of yoga in improving cognitive health, and if proven effective, the gentle and amenable nature of yoga practice could have far-reaching applications for cancer survivors, many of whom are aging adults who will experience other age-related disabilities, co-morbidities, and overall compromised physical health. If found comparable to or better than aerobic exercise, yoga practice could be recommended and promoted as an alternative form of physical activity for adult cancer survivors to improve cognition and cancer-related cognitive impairment as well as physical and psychosocial health.

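### The sample size enters Cohen's f = 0.35 as if it lay on the cited Hedges' g scale of 0.32–0.47, so the stated 80% power does not apply to the effects the protocol cites

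*Protocol article*

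**What the plan says.** The Sample size calculation section describes itself as very preliminary and meant to guide recruitment. It cites a meta-analysis of yoga and cognition with Hedges' g from 0.32 to 0.47 and continues: "We based our sample size calculations to adequately power for a small effect within this range". The inputs are an alpha of 0.05/2, "a power of 0.80" and "a conservative estimate of a medium effect size", given as f = 0.35. The result is 75 in total, 25 per arm. No test, no baseline correlation and no conversion from g to f is stated.

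The Statistical analysis section makes descriptive statistics and Cohen's d the focus. A time × group repeated-measures ANCOVA is optional, with baseline performance among the possible covariates. The Background gives feasibility and exploration as the purpose, and the limitations section looks ahead to a larger, fully powered trial.

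The closing claims go further. The Conclusions state: "Our study will determine the efficacy of yoga in improving cognitive health", and add: "If found comparable to or better than aerobic exercise, yoga practice could be recommended and promoted". The abstract's Discussion says the results will "enable us to understand the most effective physical activity modality".

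**The concern.** Hedges' g is the difference between two means in standard deviation units. Cohen's f is the standard deviation of the group means in the same units. The figure 0.35 falls numerically between 0.32 and 0.47, which makes it look like a cautious choice from the cited range, but on the f scale it is a much larger effect. The labels also conflict with each other: the target is called small in one sentence and medium in the next.

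A reader would conclude that 75 participants give 80% power for effects of the size found in earlier yoga studies. If they do not, the protocol credits the design with a property it lacks. The larger trial that the authors foresee could also inherit the same substitution.

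**Working it through.** **Inputs from the protocol.** Three arms of 25 (N = 75), alpha 0.05/2 = 0.025, target power 0.80, f = 0.35, cited g = 0.32–0.47.

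**Assumed, because not stated.** The correlation r between baseline and follow-up scores (range shown below), and the pattern of means (yoga differs from two equal arms, unless noted).

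**1. Reproduce 75.** The three-group F test has noncentrality λ = f²·N/(1 − r²) when follow-up is compared with baseline as a covariate.
- Without adjustment: λ = 0.35² × 75 = 9.19, power 66.2%; 98 participants would be needed for 80%.
- At r = 0.5: λ = 9.19/0.75 = 12.25, power 80.5% at N = 75 and 79.9% at N = 74. This lands on the protocol's figure.
- The between-group test of a two-visit repeated-measures ANOVA at r = 0.5 also gives 75, because 2/(1 + 0.5) = 1/(1 − 0.25).

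So 75 is a correct answer for f = 0.35 under an unstated correlation of about 0.5. The text does not show which test was used.

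**2. Put g and f on one scale.** With one of three equal arms differing, f = g·√2/3.
- g = 0.32: f = 0.151
- g = 0.47: f = 0.222
- f = 0.35: d = 0.35 × 3/√2 = 0.74. With two groups, d = 2f = 0.70.

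The effect entered is thus 0.74/0.47 = 1.6 to 0.74/0.32 = 2.3 times the effect cited.

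**3. Power at N = 75 for the cited range, alpha 0.025.** In each cell the first figure is for g = 0.32 and the second for g = 0.47.

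| Baseline correlation (assumed) | Three-group F | Pairwise, 25 v 25 |
|---|---|---|
| no adjustment | 12%, 27% | 13%, 27% |
| 0.5 | 16%, 37% | 17%, 35% |
| 0.6 | 19%, 43% | 19%, 41% |
| 0.8 | 35%, 72% | 34%, 68% |

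If 0.05/2 meant a per-tail level, so that two-sided 0.05 applies, the three-group F gives 19% and 37% without adjustment, and 24% and 48% at r = 0.5. Only one combination reaches the target: the omnibus test at g = 0.47 and r = 0.8, at about 81%.

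**4. Sample size for 80% at the cited range** (three-group F, alpha 0.025): 509 (g = 0.32) to 238 (g = 0.47) without adjustment, and 383 to 180 at r = 0.5.

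**5. Precision of a pairwise difference.** The 95% CI half-width is 1.96 × √(2/25) = 0.55 SD, or 0.57 with the t quantile on 48 degrees of freedom. At r = 0.6 it is multiplied by √(1 − 0.36) = 0.8, giving about 0.45. The unadjusted half-width exceeds the top of the cited range.

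**The case against.** The strongest reply is that this is a pilot. The calculation is labelled preliminary, the main analysis is descriptive, inferential tests are optional, and a fully powered trial is deferred. That stands, and it is why the remedy is wording and not a larger sample. It does not rescue the power sentence: a calculation that is reported should describe the effect it actually covers.

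Three stronger readings are tempting and are not supported.
- *That 75 is miscalculated or rests on an invalid test.* ANCOVA on follow-up is a valid between-arm test, it gives 75 at r = 0.5, and baseline performance is among the listed covariates. The 66% for an unadjusted test is no evidence of error.
- *That the power simply is 12–27%.* That holds only without baseline adjustment at alpha 0.025; the adjusted figures belong beside it.
- *That the plan will read a non-significant yoga–walking difference as comparability.* No such rule appears. The sentence in the Conclusions is conditional, and the protocol declares no margin; 0.32 is the lower end of a cited range, not a stated minimum important difference.

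One set-up gives higher power. Entering the converted f directly into a time × group interaction at r = 0.5 gives 51% to 88%. But that set-up needs only 28 participants at f = 0.35, so it is not the source of 75. A difference of g present only at follow-up is also a smaller interaction effect: change-score power at r = 0.5 is 13% to 27%.

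The lack of a dropout allowance is not counted here, since a condensed article may leave it out.

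**Conclusion.** The point holds as an error in the effect size entered, not in the arithmetic. The 80% power belongs to f = 0.35, a standardised difference of about 0.70–0.74, and it depends on an unstated correlation of about 0.5. For the cited g of 0.32–0.47, power at alpha 0.025 is about 12–27% unadjusted, 16–37% at r = 0.5, 19–43% at r = 0.6 and 34–72% at r = 0.8. These figures assume 25 analysed per arm, yoga differing from two equal arms, and independent participants.

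Separately, the unqualified promises to determine efficacy and to identify the best modality conflict with the protocol's own pilot purpose and descriptive plan.

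**What to change.** **Sample size calculation.** Delete the sentence "We based our sample size calculations to adequately power for a small effect within this range" and the word conservative. Replacement, with the assumptions labelled as such: the total of 75 is set by feasibility; it gives 80% power at alpha 0.025 for f = 0.35 (a difference of about 0.7 SD) if the baseline correlation is about 0.5; for g = 0.32–0.47, power is about 12–27% unadjusted and 16–37% at that correlation; the pairwise 95% CI half-width is about 0.55–0.57 SD unadjusted and about 0.45 SD at a correlation of 0.6; all figures are before dropout. The authors should confirm the test and correlation they actually used.

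**Abstract (Discussion) and Conclusions.** Replace the claims that the study will establish efficacy and identify the most effective modality with a statement that the pilot estimates between-arm differences with 95% CIs. Add that the absence of a significant difference will not be taken to show that yoga is comparable to walking.

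**Cost.** Wording only: no extra participants and no change to the design or the descriptive analysis. The stated power and the closing claims become less favourable.

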## Methods

### Study design

The STAY Fit trial is a three-arm randomized clinical exercise trial comparing the effects of a 12-week group-based yoga exercise, aerobic walking, and an active control (stretching and toning) on cognitive function and cardiovascular fitness among adult cancer survivors. We will randomize 75 low active adults between the ages of 30 and 70 years to one of the three conditions. All groups participate in structured group-based exercise led by certified and trained exercise leaders over the course of the 12-week intervention. Study outcomes include cognitive assessments, cardiovascular fitness, and psychosocial questionnaires administered at baseline and following the 12-week intervention.

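### The sample size paragraph claims adequate power for a small effect within Hedges' g .32–.47, but its f = 0.35 is a difference of about 0.70–0.86 SD, above that whole range

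*Protocol article*

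**What the plan says.** All the statements stand in one paragraph of the protocol article, under Sample size calculation.

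- The evidence is a meta-analysis of yoga and cognition that "indicated an effect size range of .32–.47 (Hedge’s g) favoring the yoga condition".
- The stated purpose: "We based our sample size calculations to adequately power for a small effect within this range".
- The effect entered is f = 0.35, described as "a conservative estimate of a medium effect size".
- The other inputs are "Using an alpha of 0.05/2" and "a power of 0.80".
- The result: "the desired total sample size is 75 (*N* = 25 per group) for this trial".

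Study design confirms the three arms: "We will randomize 75 low active adults between the ages of 30 and 70 years to one of the three conditions". The article gives no conversion from g to f and no correlation between the baseline and 12-week measurements. It does not say whether 0.05/2 is a two-sided split or a correction for two comparisons.

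**The concern.** Hedges' g is a difference between two means in SD units. Cohen's f is the spread of the group means divided by the SD. The two are on different scales, and the number 0.35 falls inside .32–.47 only if it is a g. As an f it is a much larger effect than any in the source. The paragraph also calls the effect small in one sentence and medium in the next, and labels as conservative a value that exceeds everything it cites.

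A reader of the paragraph will believe that 75 participants give 80% power for a yoga effect of the published size. The article draws efficacy conclusions elsewhere. The first aim in the Abstract is to assess the efficacy of yoga, and the Conclusions section considers what would follow if yoga were comparable to or better than aerobic exercise. If power is in fact low, a non-significant difference could be misread as absence of benefit or as comparability. The pilot is also meant to inform a larger trial, which would be undersized if the same planning effect were carried over.

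**Working it through.** **Inputs.** From Sample size calculation: g = .32 to .47, f = 0.35, alpha = 0.05/2 = 0.025, power 0.80, N = 75 in three equal arms. Assumed, because the article does not give it: the baseline–follow-up correlation r, taken as 0, 0.5, 0.7, 0.8 and 0.85.

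**Step 1: reproduce 75.** Noncentral F with three groups, noncentrality λ = f²·N/(1 − r²) when the baseline is used as a covariate.

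- r = 0, alpha 0.025: f = 0.35 needs N = 98. At alpha 0.05 it needs 82.
- r = 0.5, alpha 0.025: λ = 0.1225 × 75/0.75 = 12.25 and power is 0.805. The smallest N is 75.
- A between-groups test on two measurements, λ = f²·N·2/(1 + r), has the same λ at r = 0.5 (2/1.5 = 1/0.75). Power is 0.806 and N = 75.

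So 75 can be reproduced with 0.35 as a true f and an unstated correlation of about 0.5. If 0.35 were a g, an unadjusted pairwise comparison would need 130 per arm (alpha 0.05) or 157 per arm (alpha 0.025), so 75 does not follow on that reading.

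**Step 2: put f = 0.35 in SD units.**

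- Two groups, d = 2f: 0.70, and 0.70/0.47 = 1.5.
- Three arms, yoga apart from two equal arms, d = 3f/√2: 0.74, and 0.74/0.47 = 1.6.
- Three arms evenly spaced, d = f·√6: 0.86 between the extremes, and 0.86/0.47 = 1.8.

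**Step 3: put the cited range on the f scale.**

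- Two groups, f = g/2: 0.160–0.235.
- Yoga apart, f = g·√2/3: 0.151–0.222.
- Evenly spaced, f = g/√6: 0.131–0.192.

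Overall this is about 0.13–0.24. The two-group conversion is the most favourable; the other two are the three-arm patterns.

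**Step 4: omnibus power at N = 75, alpha 0.025.** Each cell gives evenly spaced / yoga apart / two-group.

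| assumed r | g = .32 | g = .47 |
|---|---|---|
| 0 | 0.094 / 0.122 / 0.136 | 0.197 / 0.268 / 0.305 |
| 0.5 | 0.122 / 0.161 / 0.182 | 0.268 / 0.365 / 0.413 |
| 0.7 | 0.178 / 0.242 / 0.275 | 0.404 / 0.537 / 0.597 |
| 0.8 | 0.258 / 0.352 / 0.398 | 0.568 / 0.717 / 0.776 |
| 0.85 | 0.342 / 0.460 / 0.516 | 0.703 / 0.840 / 0.886 |

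If 0.05/2 means an F test at 0.05, the ranges become 0.153–0.413 unadjusted and 0.191–0.528 at r = 0.5. At r = 0.8 and g = .47 they are 0.678 / 0.807 / 0.853; at g = .32 the best figure is 0.513.

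**Step 5: detectable pairwise difference.** With 25 per arm, alpha 0.025 and 80% power, noncentral t gives 0.90 SD unadjusted. Multiplying by √(1 − r²) gives about 0.78 SD at r = 0.5 and 0.64 SD at r = 0.7. All three exceed 0.47.

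**The case against.** **It is a pilot.** The article notes that pilots do not usually report formal calculations, presents this one as a rough aid to recruitment planning, and in Statistical analysis puts descriptive statistics and Cohen's d first, with the time × group test only a possibility. No decision rule rests on significance. This stands as a reason for lower severity and for leaving N alone. It does not make the power statement true, and the efficacy language in the Abstract and Conclusions keeps the statement consequential.

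**The cause is not documented.** A reader might infer that the authors took a g of 0.35 and entered it as f. The coincidence of the number with the cited range suggests this, but the article never says how 0.35 was chosen. Calling 0.35 a medium effect is natural on the f scale, so it may have been a working value picked alongside the meta-analysis. The contradiction can be shown from the text; the cause cannot.

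**Power depends on the correlation.** A reader might also infer that the trial is not powered for any effect in the cited range. That goes too far. At g = .47, under the two-group and yoga-apart conversions, power is 81–85% at r = 0.8 with alpha 0.05 and 84–89% at r = 0.85 with alpha 0.025. For a pairwise contrast at g = .47 the correlation needed for 80% is about 0.81 (alpha 0.05) to 0.85 (alpha 0.025). This part of the objection stands. However, the article states no such correlation, and 75 was not derived from one: at r = 0.8 the same f = 0.35 would have needed only about 33–39 participants.

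**Conclusion.** The paragraph is wrong as written. It claims adequate power for a small effect within g .32–.47, and the effect it uses is 0.70–0.86 SD, about 1.5 to 1.8 times the top of that range. This conclusion does not depend on the correlation, the meaning of alpha or the pattern of arm means.

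The power figures do depend on them. At alpha 0.025 power over the cited range is about 9–31% unadjusted, 12–41% at r = 0.5 and 18–60% at r = 0.7; at alpha 0.05 it is at most 53% with r = 0.5. The supportable claim is that power for the cited range is not shown, that 80% at g = .47 would require an unstated correlation of roughly 0.8 or more, and that g = .32 remains underpowered at that correlation (26–40% at alpha 0.025, at most 51% at alpha 0.05). Dropout and the joint randomisation of couples or friends are left out of these figures.

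The point should be fixed, but given the pilot status it is a correction of a statement and not a challenge to the size of the trial.

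**What to change.** Revise the paragraph and keep N = 75.

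- Delete the claim "We based our sample size calculations to adequately power for a small effect within this range" and the word conservative.
- State f = 0.35 as a difference of about 0.70–0.86 SD depending on the pattern of arm means, and note that g .32–.47 corresponds to f of about 0.13–0.24.
- Say what 0.05/2 means and which baseline–follow-up correlation was assumed.
- Report power over the cited range, and the detectable pairwise difference (about 0.64–0.90 SD at alpha 0.025 for correlations from 0.7 down to 0), as conditional on the assumed correlation.
- State that 75 is a pilot size and that a non-significant difference is not evidence against an effect of the published size.

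The cost is the wording of one paragraph. No participants or procedures are added; the stated power becomes less favourable.
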